**Figure 2 F2:**
[figure not shown]
CaMMS trial flow diagram. CaMMS, calcium and multiple micronutrient supplement.

**Table 3 T3:** Schedule of enrolment, interventions and assessments in the CaMMS trial

	Screening	Allocation	Post-allocation					Close-out
TIMEPOINT^*^	*−t_i_* to t_0_	Baseline: 6<20 weeks	Interim ANC/HH visits	Mid-Pregnancy: 20<24 weeks	Interim ANC/HH visits	Late Pregnancy: 30<34 weeks	Interim ANC/HH visits	Birth
		(t_0_)	(t_1_)	(t_2_)	(t_3_)	(t_4_)	(t_5_)	(t_6_)
ENROLLMENT:								
Screening consent	X							
Eligibility screening (Hb testing; ultrasound)	X							
Trial consent	X							
Allocation		X						
INTERVENTION/ COMPARATOR:								
Ca and MMS Together								
Ca and MMS Separate								
ASSESSMENTS FOR WOMEN:								
Socio-demographics		X						
Food insecurity		X						
Obstetric history		X						
Dietary intake		X		X		X		
Health card data abstraction^†^		X	X	X	X	X	X	X
Anthropometry		X		X		X		
Blood pressure		X		X		X		X
Venous blood draw		X		X		X		
Point-of-care Hb testing		X		X		X		
Adherence			X	X	X	X	X	X
Morbidity		X	X	X	X	X	X	X
Pregnancy outcome								X
ASSESSMENTS FOR INFANTS:								
Anthropometry								X
Heel prick blood sampling								X
Point-of-care Hb & ferritin testing ^‡^								X

* Interim visits include: (a) routine antenatal care in Burkina Faso or household visits in Pakistan, where data will be collected and supplements dispensed; and (b) HH visits to provide counselling and measure adherence. Timepoints will vary depending on week of enrolment (eg, women enrolling at 6 weeks will have three interim ANC and 4 HH visits; women enrolling at 19 weeks will have no interim ANC and 2–3 HH visits).

† Abstracted data will include anthelminthic medications, sulfadoxine-pyrimethamine (Burkina Faso only), low-dose aspirin, blood transfusion, IV iron, iron-containing supplements.

‡ Point of care ferritin testing will be done for infants only.

ANC, Antenatal care; CaMMS, calcium and multiple micronutrient supplement; Hb, haemoglobin; HH, household; MMS, multiple micronutrient supplement.

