#### ANC follow-up visits

After enrolment, women will be seen by research staff every 4 weeks and encouraged to attend all recommended ANC visits. In Burkina Faso, these visits will coincide with routine antenatal care. In Pakistan, except for the 20<24 and 30<34 week visits, follow-ups will take place at the home. At each visit, adherence will be assessed by asking about supplement use on the prior day, including: whether the woman took each of the supplements, whether they were taken together or separately, at what time each of the supplements was taken, and whether each of the supplements was taken with or without food. Women will also be asked how many days in the past week they took each of the supplements. Finally, we will count and record the number of tablets remaining in the blister packs. Additional supplements will be dispensed so that women always have an 8-week supply. Staff will also collect morbidity information and abstract health card data on anthelminthic medication, sulfadoxine-pyrimethamine (Burkina Faso only), and low-dose aspirin. Providers at both sites will be trained to clearly record any blood transfusions, IV iron, and iron-containing supplements for data abstraction, and women will be asked to keep prescriptions and medication boxes. Information on all locally available iron-containing supplements, including photographs of packaging, was collected to facilitate data capture.

For visits in the windows of 20<24 and 30<34 weeks, women will also undergo a physical exam (including anthropometric measurements and blood pressure) and dietary intake assessment. The exam will include the venous blood draw, as described above. On-site Hb testing will be done using the HemoCue device for the purpose of identifying women with Hb<70 g/L and referring them for care while they are at the clinic. The primary trial outcome and safety outcome will be based on results of the CBC. These results will be reviewed after each visit to identify any cases of severe anaemia that were missed by on-site HemoCue testing. These women will be contacted and referred for care; their outcome data will be retained in the analysis. In Burkina Faso, malaria rapid diagnostic testing will also be done and, if positive, women will be referred for treatment.

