Results of ferritin, malaria and haemoglobinopathy testing will be shared with women. Women with haemoglobinopathies will be referred for counselling and medical management and monitoring. As National Pregnancy Care Guidelines in Burkina Faso contraindicate iron supplementation during pregnancy in women with SS or SC haemoglobinopathies, we will apply this exclusion to both sites. They will be deemed ineligible for the trial based on a contraindication and treated as post-randomisation exclusions. Women who are AS or AC carriers will be eligible for the trial and informed of their carrier status. Results of all tests will be kept confidential by the study team, but women will be free to share results with their care providers.

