As treatment effects may vary between countries due to differences in the determinants of Hb concentration, we will use a two-stage approach to combine treatment effect estimates across countries. In the first stage, we will estimate country-specific treatment effects and 95% CIs using simple linear regression models with a dummy variable for allocation. We will treat these site-specific analyses as separate hypothesis tests and will not correct for multiple testing across site-specific analysis results. In the second stage, we will pool the country-specific effects. Since between-country heterogeneity in treatment effects cannot be estimated precisely with only two countries, we will present both fixed-effect and random-effects estimates across countries. The latter will be performed using the inverse variance approach with the between-country treatment effect variance estimated by the DerSimonian and Laird method. Country-specific results will be the primary basis for the NI decision; the pooled estimates are secondary summaries to present the range of plausible pooled effects without relying on an imprecise estimate of between-country heterogeneity or assuming a common effect across countries. In addition to the unadjusted analyses, we will conduct sensitivity analyses including the following baseline covariates: parity, body mass index, height and baseline values for Hb, ferritin, CRP and AGP. We will follow the same approach for the ITT, PP and mITT analyses. NI will be determined using the fixed-margin methods (figure 3). That is, if the lower limit of the 95% CI around the difference in Hb concentration between the intervention and control is greater than the NI margin of −3 g/L, the intervention will be deemed non-inferior. We will use both ITT and PP approaches. For NI trials, PP analysis provides a more conservative assessment; however, as differential adherence between arms is possible, PP analysis may introduce bias through differential post-randomisation selection based on adherence. Therefore, while both analyses will be examined for consistency, ITT will be considered primary. We will also explore effect modification based on receipt of any iron treatment, extracted from health cards, and dietary iron and calcium intakes. A *p* value<0.05 for the interaction term will be considered statistically significant.

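### Effect modification is to be tested by receipt of any iron treatment without limiting it to iron received before randomisation, so the strata and the interaction are liable to post-randomisation selection bias

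*Protocol article*

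**What the plan says.** After setting out the non-inferiority analysis, Statistical methods adds: "We will also explore effect modification based on receipt of any iron treatment, extracted from health cards, and dietary iron and calcium intakes". The decision rule is that a p "value<0.05 for the interaction term will be considered statistically significant". No time window is given for the iron treatment, and no visit is named for the dietary intakes.

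Other parts of the article show when and how iron treatment arises and is recorded:

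- **Recording.** ANC follow-up visits says: "Providers at both sites will be trained to clearly record any blood transfusions, IV iron, and iron-containing supplements for data abstraction". The health-card footnote to Table 3 lists "low-dose aspirin, blood transfusion, IV iron, iron-containing supplements" among the abstracted items. Table 3 marks this abstraction at baseline and at every later timepoint, including birth.
- **Referral.** At the 20<24 and 30<34 week visits: "On-site Hb testing will be done using the HemoCue device for the purpose of identifying women with Hb<70 g/L and referring them for care". For severe anaemia found later on the complete blood count: "These women will be contacted and referred for care; their outcome data will be retained in the analysis".
- **Results given to women.** Biospecimen analysis says: "Results of ferritin, malaria and haemoglobinopathy testing will be shared with women". Women may pass these results to their providers.
- **Blinding.** Study design states that participants and staff in direct contact with them are not blinded.
- **Diet.** Table 3 marks dietary intake at baseline and at both later blood-draw visits.

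**The concern.** An effect modifier should be a characteristic that the randomised regimen cannot change. Iron treatment during follow-up is not one. It can be a response to low Hb, and Hb is what the regimen is being tested for changing. It can also depend on the behaviour of women and staff who know the allocation. Once given, it acts on the primary outcome. Splitting women by it then compares groups that randomisation did not make alike: treated women in one arm need not resemble treated women in the other.

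The same section recognises this problem for the per-protocol analysis, where it warns of bias from post-randomisation selection on adherence, and it restricts the adjusted models to baseline covariates. The effect-modification sentence carries neither the warning nor the restriction.

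At stake is the reading of an exploratory result. A difference between strata, or a significant interaction, could be reported as a finding about who tolerates co-administration when it reflects only who was treated.

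**Working it through.** **1. The plan's own figure.** From Sample size: margin 3 g/L, SD 17 g/L, one-sided alpha 0.025, power 90%, 15% loss.

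n per arm = 2 × 17² × (1.960 + 1.282)² / 3² = 674.8, so 675. Per country: 1350 / 0.85 = 1588.2, so 1589, against 1600 stated. The sample size reproduces. With 15% loss, 1600 leaves 1360 evaluable women, or 680 per arm.

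**2. Timing.** Outcome: Hb at 30<34 weeks. Modifier: any iron treatment on the health card. Abstraction: baseline through birth. As written, the modifier mixes iron before randomisation (a valid modifier), iron between randomisation and outcome (open to influence by the regimen), and iron after the outcome (which cannot modify an effect already measured).

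**3. Illustration.** Except for the SD, these inputs are assumptions and not figures from the documents: mid-pregnancy Hb has mean 105 and SD 17 g/L; the regimen effect is -3 g/L in every woman and fully present by mid-pregnancy; mid- and late-pregnancy Hb correlate at 0.6; 70% of women with mid-pregnancy Hb below 100 g/L are treated; treatment adds 8 g/L. There is no true effect modification.

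Let z = (100 - arm mean) / 17. The proportion treated is 0.7 × Φ(z). The mean deviation of treated women from their arm mean is -17 × φ(z) / Φ(z). The untreated deviation follows because deviations average to zero within an arm.

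| | Separate | Together |
|---|---|---|
| Arm mean | 105 | 102 |
| z | -0.294 | -0.118 |
| Φ(z) | 0.384 | 0.453 |
| Proportion treated | 26.9% | 31.7% |
| Deviation, treated | -16.90 | -14.86 |
| Deviation, untreated | +6.22 | +6.91 |

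- Treated stratum: -3 + 0.6 × (-14.86 + 16.90) = -1.78 g/L. The gain of 8 cancels because all women in this stratum receive it.
- Untreated stratum: -3 + 0.6 × (6.91 - 6.22) = -2.59 g/L.
- Spurious interaction: -1.78 + 2.59 = 0.81 g/L.
- ITT: -3 + 8 × (0.317 - 0.269) = -2.61 g/L.

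Since the gain cancels within strata, selection alone produces the distortion.

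**4. Sensitivity.**

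- True effect 0 with equal treatment by arm: both stratum effects are 0 and the interaction is 0.
- True effect -5 g/L, other inputs as in step 3: -3.0 treated, -4.35 untreated, interaction about 1.35 g/L.
- Threshold set at the documented referral level of 70 g/L, with every woman below it treated: Φ(-2.06) = 2.0% v Φ(-1.88) = 3.0% treated. Treated deviations are -41.23 and -38.58, so the treated effect is -3 + 0.6 × 2.65 = -1.4 g/L. Untreated deviations are 0.83 and 1.19, giving -2.8 g/L. With 680 per arm the treated stratum holds only about 14 and 20 women.
- Simulation of 680 women per arm (2000 replicates; thresholds 90, 100 or 110 g/L; 80–90% treated; gain 5 g/L; correlation 0.5 or 0.7): at -3 g/L, spurious interaction 0.5 to 0.9 g/L and rejection 5–8%; at -5 g/L, 0.9 to 1.4 g/L and 7–13%; at 0, about nil and 3–6%.

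**The case against.** The strongest reply is that this is an exploratory analysis outside every decision. The non-inferiority conclusion rests on country-specific ITT results under a treatment policy strategy, and none of that is conditioned on iron treatment. This stands, and it limits the weight of the point.

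Second, the size depends on an assumed treatment rule. The only Hb action stated is referral below 70 g/L, at which very few women would be treated. This stands as a limit on the magnitudes, but not on the definition of the modifier.

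Third, health cards are also abstracted at baseline, so a valid pre-randomisation definition is available; the full SAP or the supplemental intercurrent-event table, neither shown, may deal with iron treatment. The first part is true and makes the fix easy. The second cannot be checked, and handling iron treatment as an intercurrent event would not by itself repair an interaction test on it.

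Fourth, the dietary part is weaker: no mechanism is evident by which tablet timing would change diet, and choosing the visit could be left to the SAP. It is a clarification only.

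A reader might also infer more than the documents support:

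- *That the subgroup results are certainly biased and uninterpretable.* With no regimen effect and no arm difference in treatment, the bias is zero.
- *That the analysis could make co-administration look harmless in untreated women.* In the illustration that stratum shows -2.59 g/L, almost the ITT value of -2.61.
- *That low ferritin triggers iron treatment.* The article says only that results are shared with women, who may pass them on.

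**Conclusion.** The point holds as a flaw in how a stated exploratory analysis is defined. The modifier has no baseline limit, is recorded mainly after randomisation, can be affected by the allocated regimen or by unblinded care, and may include iron given after the outcome. Its strata and interaction cannot safely be read as effect modification.

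The bias is conditional and moderate. It arises if co-administration lowers Hb or if care differs by arm. For a true effect of -3 g/L the illustrations give a spurious interaction of about 0.5 to 0.9 g/L at treatment thresholds of 90 to 110 g/L, and about 1.4 g/L at 70 g/L in a very small treated stratum. The p<0.05 rule is little disturbed at -3 g/L (5–8% rejection), so the main risk is misleading stratum estimates. Apart from the SD of 17 g/L, the simulation inputs are assumptions. The primary ITT decision is unaffected.

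**What to change.** Define effect modifiers from baseline data only: iron use before randomisation, baseline Hb or ferritin, and iron and calcium intake from the baseline food frequency questionnaire. Remove iron treatment during follow-up as an effect modifier and report its frequency descriptively by arm. Any handling of it as an intercurrent event should be kept consistent with the supplemental estimand tables; no particular strategy is required by this point.

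The cost is a change of wording in the protocol and, if needed, the SAP. All the variables are already collected, and neither the sample size nor the visit schedule changes.

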**Figure 3 F3:**
[figure not shown]
Interpretation of noninferiority results from CIs using the fixed margins method. MMS, multiple micronutrient supplement.

If <10% of outcomes are missing due to losses to follow-up, specimen handling or testing considerations, or very preterm or extremely preterm birth prior to 30 weeks, we will perform multiple imputation by chained equations of missing outcome data using predictive mean matching to generate 50 complete datasets for ITT analysis.^46^ Multiple imputation has been proposed as a robust strategy to address outcome missingness in NI trials under the assumption that data are missing at random.^47^ Our imputation model will include, at minimum, treatment arm and covariates we have prespecified for inclusion in adjusted models. Multiple imputation will be performed within country to preserve site-specific data structures. Analyses will be repeated on each imputed complete dataset, and results will be pooled using Rubin’s method. We will conduct sensitivity analyses using inverse probability weighting to assess the robustness of conclusions to missingness if ≥10% of outcome data are missing.^48^

The analytic approach for secondary (table 1) and exploratory outcomes (table 2) will use ITT, PP and mITT to determine superiority of Ca and MMS taken together compared with Ca and MMS taken separately. We will use the same two-stage approach to analyse the countries separately and then pool country-specific treatment effects. For ferritin and soluble transferrin receptor, we will present results both unadjusted and adjusted for inflammation (CRP and AGP) using the methods published by Namaste *et al.*^34^ For binary outcomes, we will use log-binomial regression models with a log link and a binomial response distribution to estimate prevalence ratios with 95% CIs. P values will be adjusted for multiple comparisons using the Holm method, and statistical significance will be determined at α=0.05.

A full Statistical Analysis Plan is available at https://doi.org/10.17605/OSF.IO/36W58.

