### Sample size

For this NI trial, we calculated an NI margin using guidelines developed by the US Food and Drug Administration and the European Medicines Agency.^35^ Briefly, the NI margin is based on effect sizes from prior meta-analyses or trials of the active control, with the smallest expected treatment effect (M1) set at the limit of the 95% CI that is closest to the null effect. We found no studies comparing the effects of MMS and calcium taken together versus placebo, and data comparing MMS to a placebo were similarly limited. We therefore used the pooled effect size for Hb concentration at or near term (8.88 g/L (95% CI 6.96 to 10.8)) from 20 trials of iron-containing supplements, compared with the same formulations without iron, no treatment or a placebo.^36^ As the lower limit is clinically large (7.0 g/L), common practice is to preserve 50% of the minimum effect for an NI margin (M2) of −3.5 g/L. However, the absolute value of this effect exceeds 3.0 g/L, which we would consider clinically meaningful based on the difference between the third and fifth normative centiles for maternal Hb at 30<34 weeks’ gestation derived from the INTERGROWTH-21st Project,^37^ that is, the difference between a probable diagnosis of being at high risk versus anaemic. Therefore, we selected a more conservative NI margin of −3.0 g/L.

We assumed a one-sided α=0.025; 90% power; an SD of 17 g/L, based on prior data from both sites and assuming equal group variance across treatment arms^38,39^; and 15% loss to follow-up. Accordingly, a sample of 1600 women per country (3200 women in total) will be required to conclude NI, in each country independently; that is, that the lower limit of the 95% CI around the difference in Hb concentration between the intervention (MMS and Ca taken together) versus control (MMS and Ca taken separately) is greater than −3 g/L.

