### Statistical methods

The statistical analysis will be structured around three pre-specified estimands, defined in accordance with the ICH E9(R1) Addendum and described in online supplemental table 1. Anticipated intercurrent events and their handling strategies are specified in online supplemental table 2. Briefly, the primary estimand applies a treatment policy strategy across all randomised women (ITT); the secondary estimand applies a per protocol strategy restricted to adherent women; and the sensitivity estimand applies an analysis restricted to women who did not develop severe anaemia prior to outcome ascertainment (mITT). The analyses described below correspond to these three estimands.

For analysis of the primary outcome—Hb measured by haematology analyser at 30<34 weeks of gestation—we will apply all three estimands. For the per protocol analysis, we will use a two-tier approach to characterise adherence. The first tier will quantify the median pill count per monthly follow-up visit. The second tier will quantify the percentage of monthly follow-up visits and household visits where women self-reported taking calcium and MMS at the appropriate time on the previous day, that is, the time prescribed for their assigned study arm. The per protocol dataset will include subjects who consumed a median of ≥75% study supplements per month based on pill count and consumed supplements at the prescribed time on the prior day at ≥75% of visits. The mITT dataset will include subjects who were not diagnosed with severe anaemia (Hb 70 g/L) during follow-up period.

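### Multiple imputation for the ITT analysis applies only below 10% missing outcomes, yet the trial plans for 15% loss, so at the planned attrition no primary missing-data method is named

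*Protocol article*

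**What the plan says.** All from the protocol article.

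- **Statistical methods, missing outcomes.** The paragraph opens "If <10% of outcomes are missing due to losses to follow-up" and goes on to count specimen and testing problems and births before 30 weeks. Under that condition, missing outcomes are imputed by chained equations with predictive mean matching (50 datasets, within country) for the ITT analysis. Inverse probability weighting is planned as a sensitivity analysis "to assess the robustness of conclusions to missingness if ≥10% of outcome data are missing". No primary method is named for that second branch.
- **Statistical methods, imputation model.** "Our imputation model will include, at minimum, treatment arm and covariates we have prespecified for inclusion in adjusted models". Those covariates are all baseline: parity, body mass index, height, haemoglobin, ferritin, CRP and AGP.
- **Statistical methods, estimand and model.** "the primary estimand applies a treatment policy strategy across all randomised women (ITT"). The country-specific model is a simple linear regression on allocation. ITT is primary, and the non-inferiority decision rests on the country-specific results.
- **Sample size.** "We assumed a one-sided α=0.025; 90% power; an SD of 17 g/L", with "15% loss to follow-up", giving 1600 women per country; "we selected a more conservative NI margin of −3.0 g/L".

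**The concern.** The rule runs the wrong way. Missing-data handling matters least when little is missing and most when much is missing, but here imputation is promised in the first case and lapses in the second. The trial's own planning figure puts it in the second.

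A linear regression on allocation drops any woman without an outcome. With no primary method stated at 10% or more, following the text as written leaves an analysis of observed women as the primary ITT result. That departs from the declared estimand. Unless data are missing in a way that does not disturb the comparison, it can move the estimated difference towards or away from the margin. The same paragraph recommends multiple imputation as a robust approach for non-inferiority trials, so withholding it at the expected attrition does not look intended.

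The paragraph also does not say whether the 10% is judged per country or overall, although imputation and the non-inferiority decision are both by country.

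**Working it through.** **1. Reproduce the planned sample size.** Inputs from the Sample size section: margin 3 g/L, SD 17 g/L, one-sided α 0.025, power 90%, loss 15%. A true difference of 0 is assumed; it is not stated, but it reproduces the plan.

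- n per arm = 2 × (1.960 + 1.282)² × 17² / 3² = 674.8, so 675 per arm and 1350 evaluable per country.
- 1350 / (1 − 0.15) = 1588.2, so 1589, against 1600 stated. Reproduced. The Abstract's 1600 could be read as both countries together; I use the Sample size figure of 1600 per country.

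**2. Which branch does the plan expect?**

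- Planned missing: 0.15 × 1600 = 240 per country, leaving 1360 observed.
- Imputation branch: fewer than 160 missing, so at most 159.
- Binomial probability of 159 or fewer missing out of 1600: about 1.5 × 10⁻⁹ if true loss is 15%, about 0.005 at 12%, about 0.49 at 10%.

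**3. Power.** With 680 observed per arm, SE = 17 × √(2/680) = 0.922 g/L. Power = Φ(3/0.922 − 1.96) = 90.2%. With 10% missing (1440 observed) it is 91.7%.

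**4. How far could the difference move?** If women missing from one arm average D g/L different from those observed in that arm, and the other arm has no such gap, the observed-case difference shifts by 0.15 × D. For D = 3, 5 or 10 the shift is 0.45, 0.75 or 1.5 g/L, against a 3 g/L margin.

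**5. Error at the margin under different loss patterns.** Assumptions, none given in the protocol: true difference −3.0; correlation 0.6 between haemoglobin at 20<24 and 30<34 weeks; 15% missing in each arm; the log-odds of loss rise by a slope b for each SD decrease in mid-pregnancy haemoglobin. SD 17 is from the plan. Large Monte Carlo samples give the observed-case difference (repeat runs agree within about 0.03 g/L). One-sided error = Φ(bias/0.922 − 1.96).

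| b, together arm | b, separate arm | Observed-case difference | Bias | One-sided error |
|---|---|---|---|---|
| 0.25 or 0.5 | same | about −3.0 | about 0 | about 2.5% |
| 0.5 | 0.25 | −2.62 | +0.38 | about 6% |
| 0.25 | 0 | −2.63 | +0.37 | about 6% |
| 0.5 | 0 | −2.24 | +0.76 | about 13% |
| 0 | 0.25 | −3.37 | −0.37 | about 0.9% |
| 0 | 0.5 | −3.76 | −0.76 | about 0.3% |

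To put the slopes in g/L: a bias of 0.76 with 15% missing means lost together-arm women average about 0.76/0.15 = 5 g/L below those observed.

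**6. Does the choice of variables matter?** In the third and fourth rows, imputing from baseline haemoglobin alone (baseline correlations also assumed) left −2.83 and −2.60; adding the 20<24-week value recovered −3.0. Inverse probability weighting on mid-pregnancy haemoglobin also recovered about −3.0.

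**The case against.** Several points on the other side are sound.

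- **No complete-case analysis is stated.** A reader might say that the plan prescribes one. It does not: the method at 10% or more is left unnamed, and using observed women only follows from the regression model. The supplemental estimand tables and the SAP are not shown and may name a method. What stands is that the article itself sets a rule, and that rule does not fit its own loss assumption. Reading it as imputation continuing above 10% contradicts the condition it sets.
- **15% is an allowance, not a forecast.** True, and loss may be lower. But the trigger also counts specimen failures and early births, and the primary method should not depend on doing better than planned.
- **Safeguards exist.** Weighting is prespecified at 10% or more and can remove the same bias if it uses mid-pregnancy haemoglobin. The covariate-adjusted analysis also helps when loss depends on baseline values. A reader might infer that large missingness would go unexamined; it would not. Both are sensitivity analyses, however, and do not decide non-inferiority.
- **The imputation model is a floor.** A reader might infer that mid-pregnancy haemoglobin is excluded. The wording sets a minimum and permits adding it; it simply does not require it.
- **Inflated error is not a prediction.** The 6–13% figure needs loss that depends on low haemoglobin only, or more strongly, in the together arm. Nothing in the protocol supports that asymmetry. The Interventions section expects the separate regimen to be the harder one to follow, and other patterns give no bias or a conservative one.
- **Different methods in the two countries** are possible only if the 10% is judged by country, which the text leaves open.

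**Conclusion.** The point holds in this form: the missing-data rule conflicts with the trial's own planning. At the planned 15% loss the imputation branch would practically never apply (240 expected missing against at most 159), no primary method replaces it, and the default is a regression on observed women despite an estimand covering all who were randomised.

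Power is not harmed, at about 90% per country with 1600 enrolled. The exposure is bias of unknown direction. Under the stated assumptions, one-sided error at the margin runs from below 1% to about 13%, with about 2.5% when loss depends on haemoglobin equally in both arms. This is a should-fix matter: a flaw in a stated rule, cheap to correct, with planned sensitivity analyses that would give some warning.

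**What to change.** 1. Delete the 10% trigger. State that multiple imputation within country is the primary ITT handling at any level of missingness. This also removes the question of whether the cut-off is per country or overall.
2. Name the 20<24-week CBC haemoglobin in the imputation model, alongside treatment arm and the baseline covariates. It is already collected.
3. Keep inverse probability weighting and the observed-case analysis as sensitivity analyses whatever the missing fraction.
4. Optional: a delta-adjusted imputation run to show how far departures from missing at random would have to go to change the conclusion.

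Items 1–3 follow from the defect or directly support its repair; item 4 is a matter of preference. The cost is a wording change in the protocol and SAP and a little programming, with no new data and no change to the sample size. It should be settled before unblinding.

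### Multiple imputation for the ITT analysis is allowed only below 10% missing outcomes, yet the trial is sized for 15% loss, and the article names no primary method for that case

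*Protocol article*

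**What the plan says.** All references are to the protocol article.

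- **Statistical methods, missing-data paragraph (after Figure 3).** The condition is "If <10% of outcomes are missing due to losses to follow-up, specimen handling or testing considerations", with birth before 30 weeks as a further cause. When it is met, "we will perform multiple imputation by chained equations of missing outcome data using predictive mean matching to generate 50 complete datasets for ITT analysis". The imputation model holds at least treatment arm and the covariates of the adjusted models (these include baseline haemoglobin), and it is run within country.
- **Same paragraph, the other branch.** "We will conduct sensitivity analyses using inverse probability weighting to assess the robustness of conclusions to missingness if ≥10% of outcome data are missing". Nothing else is said about 10% or more.
- **Sample size.** "We assumed a one-sided α=0.025; 90% power; an SD of 17 g/L, based on prior data from both sites", "and 15% loss to follow-up". The result: "a sample of 1600 women per country (3200 women in total) will be required to conclude NI, in each country independently". On the margin: "Therefore, we selected a more conservative NI margin of −3.0 g/L".
- **Statistical methods, estimands.** "the primary estimand applies a treatment policy strategy across all randomised women (ITT").
- **Statistical methods, primary model.** Each country is analysed by linear regression on an allocation indicator alone. Models with baseline covariates are sensitivity analyses. The country-specific results are the main basis for the non-inferiority decision. ITT is primary, and per protocol is examined beside it for consistency.

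**The concern.** The threshold for imputation lies below the loss the trial was sized to absorb. If loss is as planned, the one missing-data method specified for the ITT analysis does not apply, and what replaces it is labelled a sensitivity analysis. No other primary method is named. The primary regression then runs, by default, on women with an observed haemoglobin at 30<34 weeks, although the estimand is defined for every woman randomised.

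The rule also runs the wrong way. The distortion that missing outcomes can cause grows with the fraction missing, so imputation is used where it matters least and withdrawn where it matters more.

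At stake is the estimate that decides non-inferiority in each country against a margin of only 3 g/L. Participants know their regimen, and the two regimens differ in complexity, so equal loss for equal reasons in both arms cannot be taken for granted.

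**Working it through.** **Inputs from the article:** margin 3 g/L, SD 17 g/L, one-sided α 0.025, power 90%, 1:1 allocation, 15% loss, 1600 women per country, trigger <10%. **Assumed:** true difference 0 for the sample size (not stated, but needed to reproduce it). For step 4 also: baseline–outcome haemoglobin correlation 0.5, and loss depending on baseline haemoglobin as described there.

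**1. The plan's own figure.** n per arm = 2 × 17² × (1.960 + 1.282)² / 3² = 674.8, so 675. Per country 1350; 1350 / 0.85 = 1589, rounded to 1600. The stated size reproduces.

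**2. Trigger against planned loss.**

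| | Missing per country, of 1600 |
|---|---|
| Most that still permits imputation (<10%) | 159 |
| Planned loss (15%) | 240 |

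If each woman's chance of a missing outcome is 15%, the binomial probability of 159 or fewer missing is about 1.5 × 10⁻⁹; at 12% it is 0.5%. Failed specimens and births before 30 weeks also count as missing, so the total could exceed the loss to follow-up.

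**3. Power is not the issue.** Power = Φ(3 / SE − 1.96), with SE = 17 × √(2 / n per arm).

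| Missing | Observed per arm | SE (g/L) | Power |
|---|---|---|---|
| 10% | 720 | 0.896 | 91.7% |
| 15% | 680 | 0.922 | 90.2% |
| 20% | 640 | 0.950 | 88.4% |

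**4. Possible bias in the observed-only comparison.** In one arm, the observed mean minus the full mean equals d × (mean of observed − mean of missing), where d is the fraction missing. The bias in the difference is that quantity in the together arm minus the same quantity in the separate arm.

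Suppose 15% are missing in each arm. In one arm the odds of loss double per SD lower baseline haemoglobin; in the other, loss is random. Numerical integration puts the observed women in the affected arm 0.098 SD above that arm's full baseline mean. The outcome shift is 0.5 × 17 × 0.098 = 0.83 g/L; simulation gives 0.83 to 0.85.

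- *Informative loss in the together arm:* bias about +0.85. False non-inferiority at a true −3 g/L ≈ Φ(0.83 / 0.922 − 1.96) = Φ(−1.06) ≈ 14%, against a nominal 2.5%.
- *Informative loss in the separate arm:* bias about −0.85. False non-inferiority ≈ Φ(−0.90 − 1.96) = Φ(−2.86) ≈ 0.2%. Power at a true difference of 0 falls to about Φ((3 − 0.83) / 0.922 − 1.96) = Φ(0.39) ≈ 65%.
- *Same mechanism and amount in both arms:* bias about 0, false non-inferiority about 2.2–2.5%.
- *Same mechanism (log odds ratio 0.5 per SD), unequal amount:* 18% lost in together and 12% in separate gives about +0.25 g/L and 4.7%. Reversed, it gives −0.24 g/L and 1.4%.

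Conditioning on baseline haemoglobin brought the bias to about 0 and false non-inferiority to 2.3–2.6%. Normal-model imputation on arm and baseline haemoglobin, with the loss in the together arm, gave bias 0.00 and 2.2%.

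**5. The inversion.** A 0.83 g/L shift at 15% missing implies a gap of 0.83 / 0.15 = 5.5 g/L between observed and missing women. With the same gap, 5% missing shifts the mean by only 0.05 × 5.5 = 0.28 g/L. The rule imputes in the second case and not in the first.

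**The case against.** **The complete-case fallback is not written down.** Correct. A reader might infer that the plan prescribes an observed-only comparison at 10% or more. No sentence says so, and the full statistical analysis plan and the supplementary estimand tables, which are not shown, may name a primary method. This limits the claim to what the article states and leaves as the default. It does not excuse a printed trigger that conflicts with the article's own sample-size assumption.

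**15% is an allowance, not a forecast.** Also correct, and actual loss could be lower. But a missing-data rule should work in the scenario the trial was sized for.

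**The error need not favour non-inferiority.** A reader might infer that the rule inflates false claims. The documents do not support a one-sided reading. The strengths and limitations box and the Interventions section place the added complexity and adherence risk in the separate arm. If loss follows that burden, the error runs against non-inferiority. Tablet numbers and visit schedules are the same in both arms, so informative loss in one arm only is an extreme case.

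**Safeguards exist.** The adjusted models, which include baseline haemoglobin, and the weighted analysis could expose a discrepancy. They are sensitivity analyses, though, and do not decide non-inferiority.

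**Imputation is not a cure-all.** The illustration makes loss depend on baseline haemoglobin and then conditions on it. The article itself limits imputation to missing at random, and nothing here shows that it would correct other mechanisms.

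**ITT does not stand quite alone.** A reader might say that ITT alone decides. The article makes it primary but examines per protocol for consistency.

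**Conclusion.** The point stands in this form: the printed rule switches imputation off at the trial's own planned loss (240 missing per country against at most 159 allowed) and names no primary ITT method there. The default that remains does not match an estimand for all randomised women. This follows from the text and needs no simulation.

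The numerical consequence is conditional. It is nil if loss has the same amount and mechanism in both arms. In the one-arm illustration it is about 0.85 g/L in either direction, some 28% of the margin (0.85 / 3). Those sizes rest on the assumed correlation, odds ratio and one-arm mechanism; they bracket what could happen and do not predict it. The defect concerns bias and the estimand, not sample size or power.

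**What to change.** - Delete the 10% condition. Make within-country multiple imputation the primary ITT analysis at any level of missingness, in both countries alike, with the imputation model already described.
- Run inverse probability weighting as a sensitivity analysis in every case.
- Report the observed-only comparison as supportive.
- If the full statistical analysis plan already names a primary method at 10% or more, bring the two documents into agreement.

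The cost is a change of wording before unblinding and a little more analysis. No new data are needed. The sample size stays at 1600 per country, and the 1360 women expected to be observed still give 90.2% power.
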